## Abstract

**Background:**

The COVID-19 pandemic is negatively impacting the mental health of both patients with COVID-19 and the general population. As current guidelines are limiting in-person contacts to reduce the spread of the virus, the development of a digital approach to implement in psychiatric and psychological consultations is needed. In this paper, we present the DigiCOVID protocol, a digital approach to offer remote, personalized psychological and psychiatric support to former or current patients with COVID-19 and their relatives.

**Objective:**

The main goal of this project is to evaluate the feasibility, acceptability, and usability of the DigiCOVID protocol. Furthermore, we also aim to assess the impact of the abovementioned protocol by means of pre-post changes in psychological clinical variables.

**Methods:**

Participants undergo an initial telephonic screening to ensure inclusion criteria are met. Secondly, participants complete a video-assisted neuropsychological IQ test as well as web-based self-reports of health and general well-being. Participants are then assigned to a psychotherapist who offers 8 teletherapy sessions. At the end of the therapy cycle, the web-based questionnaires are administered for a posttreatment evaluation.

**Results:**

As of April 2022, we enrolled a total of 122 participants, of which 94 have completed neuropsychological tests and web-based questionnaires.

**Conclusions:**

Our study aims at testing the feasibility and preliminary efficacy of DigiCOVID, a remote telemedicine protocol for the improvement of psychological and psychiatric health in patients with COVID-19 and their relatives. To date, the approach used seems to be feasible and highly customizable to patients’ needs, and therefore, the DigiCOVID protocol might pave the way for future telepsychiatry-based interventions.

**Trial Registration:**

ClinicalTrials.gov NCT05231018; https://clinicaltrials.gov/ct2/show/NCT05231018?term=NCT05231018 &draw=2&rank=1

**International Registered Report Identifier (IRRID):**

DERR1-10.2196/39080

## Introduction

The COVID-19 pandemic caused by SARS-CoV-2 virus is an unprecedented event both for the general population and health care workers.

Northern Italy has rapidly emerged as one of the epicenters of the first COVID-19 outbreak. The hospital in which our trial was designed and implemented, the Fondazione Istituto di Ricerca e Cura a Carattere Scientifico (IRCCS) Ca’ Granda Ospedale Maggiore Policlinico in Milan, was completely reorganized to face new cases in the intensive care unit, paralleled by a large-scale optimization of the entire health care system [1,2].

Current literature is focusing on the connections between COVID-19 and psychiatry, in particular concerning the development of posttraumatic stress disorder and related conditions in patients who contracted the disease [3]. Furthermore, evidence suggests that the pandemic itself might be a potential trigger for various other mental health diseases in the general population, with higher rates of psychological deterioration [4], a probable impact on the development of first episodes of psychosis [5], obsessive compulsive disorder [6], depression [7], anxiety [8], phobic behaviors [9], addictions [10], and general health care workers distress [11,12].

In such a historical moment, it appears of paramount importance to prevent rather than treat psychological distress with every possible means available despite the limitations associated with in-person visits, social distancing, and isolation [13,14]. In fact, current ‘shelter-in-place’ guidelines and restrictions implemented by the public health system to limit the diffusion of the virus are significantly reducing in-person psychological and psychiatric consultations [15]. On the 24th of March 2020, the Ministry for Technological innovation and Digitalization, the Ministry of Health, the National Institutes of Health, and the World Health Organization together published a formal invitation to use telemedicine technologies more thoroughly in clinical practice [16].

A multitude of digital approaches have been tentatively operationalized worldwide to meet clinical needs, with COVID-19 serving as a catalyst for a change in the way instruments are used daily in health care settings [17]. Telepsychiatry, an innovative approach that consists of remote consultations and evaluations for mental health symptoms, has become a reliable alternative to face-to-face assessments, thus adapting rather than succumbing to COVID-19 [18,19], and assisting those affected by the psychosocial consequences of the pandemic [20].

Aside from patients with COVID-19, the psychological aftermath of this pandemic to a similar degree interests those who have not contracted the virus but have clinical conditions to manage, have lost family members or peers, are unable to enjoy the physical presence of their families, and have been living in restricted conditions for months. This phenomenon is likely due to the general psychological impact of the pandemic event per se and the systemic modifications in family relationships, with high amounts of stress also in healthy relatives [21,22]. Incidence and prevalence of psychological distress have been skyrocketing beyond the possibilities of any mental health system to intervene with in-person services. This segment of the population has profound unmet clinical needs and increasingly requests access to psychiatric services.

In this paper, we aim to describe DigiCOVID, a digital mental health protocol designed to offer remote, personalized support to former or current patients with COVID-19 and their relatives. DigiCOVID includes psychotherapy sessions and psychiatric consultations depending on participants’ needs. An observational longitudinal study in patients with COVID-19 and their relatives is being conducted to investigate whether the intervention described above is feasible, usable, and acceptable for the target population. Outcome measures include engagement rates with psychotherapy sessions and psychiatric consultations, overall program completion rates, reported adverse effects, usability ratings, and clinician burden. The secondary objectives aim to (1) evaluate whether DigiCOVID induces changes in self-reports of anxiety, depression, insomnia, trauma, and quality of life and (2) determine whether DigiCOVID impacts patients with COVID-19 and their family members differently.

## Methods

### Overall Design and Timeline

The study is conducted jointly by the units of pneumology, internal medicine, psychiatry, and the laboratory of brain injury and therapeutic strategies of the Istituto di Ricerche Farmacologiche Mario Negri. Before accessing DigiCOVID, participants are taken through the following steps: first, participants undergo an initial screening to ensure the main inclusion criteria are met. Then, 2 trained neuropsychologists remotely perform neuropsychological tests on patients via Zoom. The tests are aimed at assessing patients’ IQ through the Test di Intelligenza Breve (Italian for brief intelligence test) [23] and standard progressive Raven matrices [24]. Suicidality is assessed via the Columbia Suicide Severity Rating Scale [25]. Finally, participants complete a battery of web-based self-reports that include the following: the 12-item General Health Questionnaire [26], the Impact of Event Scale–Revised [27], the 7-item General Anxiety Disorder assessment [28], the Insomnia Severity Index [29], and the 9-item Patient Health Questionnaire [30]. After completing these assessments, participants are assigned to a trained psychotherapist who offers 8 teletherapy sessions carried out through Zoom.

This model is designed to be applied to patients with COVID-19 during hospitalization, after discharge, as well as during the remission and recovery phases. Similarly, this model is intended to be delivered to people who are dealing with the hospitalization or discharge after COVID-19 of a family member or have lost a family member due to COVID-19. A total of 8 remote, 50-minute, individual psychological sessions are offered weekly using secure videoconferencing software. The severity of the clinical conditions of patients with COVID-19 has largely influenced the sequencing of the intervention.

During all phases of the clinical work, suffering is contextualized both in the light of the recent traumatic experience (eg, bereavement, hospitalization in intensive care, and fear for one’s life or that of a relative) and in the light of historical ways of suffering, so that the patient is able to recognize the meaning of the symptoms experienced.

We considered it appropriate to circumscribe the exploration of different psychological targets within each session, given the unpredictable nature of the course of illness and the possible onset of events that radically change the psychological state of patients and family members. What follows is a very schematic summary that refers to the ‘ideal’ situation, where clinical conditions (of the patient or of the relative of the patient) evolve linearly toward recovery.

Session 1 includes introductions, the exploration of the patient’s current experience, identification of the areas of suffering, and a brief recapitulation of the patient’s pre–COVID-19 psychological functioning. Session 2 attempts to define shared goals for the therapeutic process and creates an initial diagnostic framework to identify unprocessed or unregulated emotions. Session 3 aims to validate the intrapsychic and interpersonal resources associated with a greater degree of adaptation to the stressful situation, including a flexible personality; positive beliefs about the self; identity roles, acceptance, and commitment skills; work functioning; and a solid network of friends, family, or loved ones. In sessions 4 through 6, areas of clinical concern are addressed, and defense mechanisms are investigated. Session 7 aims to integrate the lived experience in the cohesive narrative of the self. In session 8, internal working models or relational patterns that have emerged during therapy closure are discussed, and psychoeducation on relapse prevention is offered. At the end of the abovementioned cycle, participants repeat the battery of web-based self-reports.

This paper follows the SPIRIT guidelines for the trial’s publication, as suggested by the EQUATOR Network. The trial is registered on ClinicalTrials.gov (NCT05231018). Of note, the protocol has been registered as it was designed at the beginning of the project, that is, it did not include relatives but only patients. Given the high number of requests, and because the intervention is customizable to each patient’s clinical needs, we have decided to extend our intervention to relatives, thus explaining the differences between the registered protocol and this methodological paper. Regarding the gap between the registration and the trial start, the internal organization of our research unit does not require the registration of trials that do not involve drugs and placebos. Therefore, the trial has been registered on ClinicalTrials.gov to improve the recruitment process.

### Study Population

Our population of interest includes patients with COVID-19, either previously or currently hospitalized at the Foundation IRCCS Ca’ Granda Ospedale Maggiore Policlinico, and their relatives, according to our inclusion and exclusion criteria.

#### Inclusion Criteria

The inclusion criteria for our study are as follows: (1) age 18-80 years; (2) a positive COVID-19 test at the moment of enrolment for participants in the ‘patients’ group; (3) adequate sensory and motor abilities, without impairments in vision and hearing or handling devices; (4) access to wireless internet technologies; and (5) a good level of Italian in terms of speaking, reading, and writing.

#### Exclusion Criteria

The exclusion criteria for this study are the following: (1) present or past medical history of schizophrenia, schizoaffective disorder, delusional disorder, bipolar disorder, or current substance abuse, all according to the Diagnostic and Statistical Manual Fifth Edition [31]; (2) a diagnosis of cognitive impairment or dementia (eg, mild cognitive impairment, Alzheimer disease, or Parkinson disease); (3) intellectual disability defined by a total IQ <70 as obtained by the Test di Intelligenza Breve [23] or the standard progressive Raven matrices [24]; (4) severe present medical conditions that could interfere with participation; (5) present or past suicidal ideation or commitment; (6) significant impairment in the use of digital and technological devices, questionnaires and test completions, as well as comprehension, or lack of a compliant behavior in the earliest evaluations; and (7) being enrolled in other clinical trials assessing any psychological or experimental pharmacological treatment.

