#### Recruitment

As of April 2022, 122 participants have been referred to the study. Participation is voluntary, and an extended informed consent form is signed before any evaluation, assessment, or voice and video call. Consent forms are collected remotely for those who have been discharged and are currently in remission and in person for those hospitalized in a COVID-19 ward of either pneumology, internal medicine, or infectious disease departments.

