### Primary and Secondary Outcome Measures

#### Primary Outcome Measures

Efforts will be made to assess all participants who have completed the minimum required intervention activities. For DigiCOVID, the minimum required intervention activities include attending psychotherapy sessions at least 4 times. As the main goal of this project is to evaluate the feasibility, acceptability, and usability of DigiCOVID, we will conduct an analysis of the following primary outcome measures in all intention-to-treat (ITT) participants:

Assessment completion rate—based on our previous studies, we expect ≥80% of participants will complete the battery of web-based self-reports.Usability ratings obtained post DigiCOVID via a 7-point Likert scale questionnaire (ie, mean rating of all responses)—this is a brief and embedded poststudy questionnaire on program satisfaction, clarity, and perceived benefits. Participants will rate each sentence on the following 7-point Likert scale: 1=completely agree; 2=mostly agree; 3=somewhat agree; 4=undecided; 5=somewhat disagree; 6=mostly disagree; and 7=completely disagree. Based on our previous studies, we hypothesize exit survey ratings of at least ≥4.5 (SD 1.5) on the 7-point Likert scale items.Reported side effects (ie, raw score)—based on our previous findings, we expect 0 adverse events due to program use.Overall program completion rate—based on previous findings, we hypothesize full program completion in ≥70% study participants.

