### Limitations

Some limitations have emerged as we operationalized this project. First, we observed a lack of motivation in some patients, likely caused by the remote technology-based approach. Second, even if telepsychiatry has been proven efficacious in assessing patients remotely, psychologists and psychiatrists are asked to adapt their methods of assessment, diagnosis, and treatment to new means of communication. The dissemination of this digital approach at a national level may require additional training for mental health professionals to ensure impact and effectiveness of this promising intervention.

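### Exclusion criterion 6 lets consented early non-compliers be recorded as ineligible instead of as feasibility failures, although completion rates are primary outcomes

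*Protocol article*

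**What the plan says.** All references are to the protocol article.

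- **Exclusion Criteria, item 6.** One limb excludes for "significant impairment in the use of digital and technological devices, questionnaires and test completions, as well as comprehension". The next limb excludes for "or lack of a compliant behavior in the earliest evaluations". Neither has a definition or threshold, and the article does not say who makes the judgement.
- **Recruitment.** "an extended informed consent form is signed before any evaluation, assessment, or voice and video call".
- **Overall Design and Timeline.** The pre-therapy steps are screening, remote neuropsychological tests and the web-based self-report battery. A therapist is assigned after these. The battery is repeated at the end of the therapy cycle.
- **Primary Outcome Measures.** The stated purpose is that "the main goal of this project is to evaluate the feasibility, acceptability, and usability of DigiCOVID". Two of the four primary measures are completion rates: "we expect ≥80% of participants will complete the battery of web-based self-reports" and "we hypothesize full program completion in ≥70% study participants". The other two are usability ratings and side effects. All four are to be analysed in the population labelled ITT.
- **Data Analysis.** That population consists of participants who reached four or more therapy sessions.
- **Limitations.** "we observed a lack of motivation in some patients, likely caused by the remote technology-based approach".

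**The concern.** In an efficacy trial, screening out people who comply poorly at the start can be a defensible choice that costs generalizability. Here the main question is whether people will and can use a remote programme, so poor engagement with its first steps is part of what is being measured.

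The clause gives the study two places to record the same event. A consented person who does not engage with the early evaluations may be a non-completion or an ineligible participant, and nothing in the criterion separates the two. Each such person recorded as ineligible drops out of any denominator restricted to eligible participants. The authors report low motivation that they link to the remote format, so the kind of behaviour the clause could capture did occur in this study.

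At stake is whether a rate that meets the 70% or 80% benchmark describes the target population or only people who had already shown that they comply.

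**Working it through.** The article states no figure for the effect of this clause, so there is nothing to reproduce. The check is about mechanism and sensitivity.

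**1. Is the clause applied after consent?** Yes. Consent precedes any evaluation or call (Recruitment), and the clause refers to behaviour in evaluations.

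**2. What does it do when the denominator is all eligible participants?** Let *c* be completion among all who consent, *e* the fraction excluded under the clause, and *q* the completion the excluded would have had. The reported rate is

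(c − e·q) / (1 − e).

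The article gives none of these three, so the values below are assumptions, set against the 70% program-completion benchmark:

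| c | e | q = 0 | q = 0.2 | q = 0.4 |
|---|---|---|---|---|
| 60% | 15% | 0.60/0.85 = 70.6% | 0.57/0.85 = 67.1% | 0.54/0.85 = 63.5% |
| 65% | 10% | 0.65/0.90 = 72.2% | 0.63/0.90 = 70.0% | 0.61/0.90 = 67.8% |

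The rate rises whenever q is below c. The size depends strongly on q, and q = 0 is the extreme case.

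**3. What does it do under the denominator the article actually plans?** Let N4 be the number who would reach four sessions if the clause did not exist, C the completers among them, and E the number excluded. Of those excluded, a fraction *a* would have reached four sessions and a fraction *q* (at most *a*) would have completed. The reported rate is

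(C − q·E) / (N4 − a·E).

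If none of the excluded would have reached four sessions, then a = q = 0 and the rate is C/N4, exactly as without the clause. The clause changes the rate only through people who complied poorly at the start and would still have attended four sessions. That group is probably small. So while the four-session rule stands, the two filters largely remove the same people.

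**4. What if only the four-session rule is corrected?** The denominator becomes all eligible participants. People removed under criterion 6 are still labelled ineligible, so step 2 applies in full. Correcting one filter does not remove the other.

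**5. Do the recruitment counts size the effect?** Results gives 122 enrolled and 94 with completed tests and questionnaires: 94/122 = 77.0%, which leaves 28 (28/122 = 23%). If 5 of the 28 were taken out as ineligible, the figure would be 94/117 = 80.3%; with 4 taken out it would be 94/118 = 79.7%. This shows only how few reclassifications separate such a figure from the 80% benchmark. It is not an estimate, because:

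- Recruitment describes the same 122 as referred, whereas Results describes them as enrolled;
- the 94 also required the neuropsychological tests;
- recruitment was still being completed, so some of the 28 may have been pending;
- others may have met a different exclusion criterion.

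**6. Is the battery in the primary outcome the one given at the early evaluations?** The article does not fix the time point. Therapist assignment follows the baseline battery, so among people with four sessions a baseline rate would be close to 100% by construction. The post-treatment battery is the more coherent reading. In that case the clause acts on the assessment outcome indirectly, by removing people whose early behaviour predicts later non-completion.

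**The case against.** The strongest objection is that the clause hardly matters as the plan is written. The primary outcomes are analysed only in people with four or more sessions, and someone who fails at the first evaluations would rarely get that far. Step 3 confirms this, and the point stands: deleting the clause alone would barely move the reported rates. It does not dispose of the concern, because once the four-session denominator is corrected the clause becomes the remaining route by which failures leave the count.

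It can also be said that a condensed article leaves operational definitions and participant-flow reporting to the full protocol. That is fair for the missing definition of compliance, which would not be a finding by itself. The finding rests on a rule that is stated and that works against the stated main goal.

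Three stronger readings are tempting, and the documents do not support them:

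- A reader might infer that the clause by itself lifts a sub-benchmark rate to 70%, for example 63% to 70% when 10% are removed (0.63/0.90). That needs an all-consented denominator, which the plan does not use, and zero completion among those removed.
- A reader might infer that the 28 of 122 were removed under this clause. Nothing links them to it.
- A reader might infer that the poorly motivated patients in Limitations were excluded. The article does not say so, nor when the lack of motivation was seen, and it discloses the observation openly.

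Finally, the article does not claim that its result already applies to everyone. Use in COVID-19 wards is offered as a possible future direction, and wide dissemination is conditional on success.

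**Conclusion.** The concern holds in a limited form. Criterion 6 permits exclusion after consent on an undefined judgement of compliance, in a study where two of the four primary outcomes are completion rates. It therefore selects on behaviour closely tied to the outcome, biases completion upward and narrows the population to which the result applies. The direction rests on one assumption: that people excluded under the clause would complete less often than the rest.

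The size cannot be computed from the article. Under the current four-session population the added effect is probably small, because the two filters overlap. Under a corrected denominator it could be several percentage points: in the assumed scenarios of step 2 the rise runs from 2.8 points (65% to 67.8%) to 10.6 points (60% to 70.6%).

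**What to change.** 1. For assessment completion and program completion, use as denominator all consented participants who meet the other eligibility criteria.
2. Count anyone removed after consent under the compliance limb of criterion 6 as a non-completion for both rates, and report how many there were. The neighbouring limb on difficulty with devices and questionnaires can describe the same behaviour, so state which limb was applied to each person.
3. Drop the compliance limb for any further enrolment.
4. Make these changes together with the change to the four-session denominator. Neither change is enough without the other.

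No new data collection is needed if the reason for each exclusion was recorded, which the article does not state. The cost is slightly lower feasibility rates. For people already removed the count is also conservative: the reported rate becomes c − e·q, so with c = 60%, e = 15% and q = 0.2 it is 57% instead of 60%. Reporting the number removed lets readers judge that difference.
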